# Investigating non-inferiority of internet-delivered versus face-to-face cognitive behavioural therapy for insomnia (CBT-I): a randomised controlled trial (iSleep well)

**DOI:** 10.1186/s13063-024-08214-6

**Published:** 2024-06-10

**Keywords:** Insomnia, CBT-I, Cognitive behavioural therapy for insomnia, Internet-delivered, Digital, Face-to-face, Non-inferiority trial, Randomised controlled trial, Guided internet intervention

## Abstract

**Background:**

Insomnia is a highly prevalent disorder associated with numerous adverse health outcomes. Cognitive behavioural therapy for insomnia (CBT-I) is recommended as first-line treatment by clinical guidelines but is accessible to only a minority of patients suffering from insomnia. Internet-delivered CBT-I (iCBT-I) could contribute to the widespread dissemination of this first-line treatment. As there is insufficient evidence regarding non-inferiority, this study directly aims to compare therapist-guided internet-delivered versus face-to-face CBT-I in terms of insomnia severity post-treatment. Furthermore, a health-economic evaluation will be conducted, and potential benefits and disadvantages of therapist-guided iCBT-I will be examined.

**Methods:**

This study protocol describes a randomised controlled two-arm parallel-group non-inferiority trial comparing therapist-guided iCBT-I with face-to-face CBT-I in routine clinical care. A total of 422 patients with insomnia disorder will be randomised and treated at 16 study centres throughout Germany. Outcomes will be assessed at baseline, 10 weeks after randomisation (post), and 6 months after randomisation (follow-up). The primary outcome is insomnia severity measured using the Insomnia Severity Index. Secondary outcomes include depression-related symptoms, quality of life, fatigue, physical activity, daylight exposure, adverse events related to treatment, and a health-economic evaluation. Finally, potential moderator variables and several descriptive and exploratory outcomes will be assessed (e.g. benefits and disadvantages of internet-delivered treatment).

**Discussion:**

The widespread implementation of CBT-I is a significant healthcare challenge. The non-inferiority of therapist-guided iCBT-I versus face-to-face CBT-I will be investigated in an adequately powered sample in routine clinical care, with the same therapeutic content and same level of therapist qualifications provided with both interventions. If this trial demonstrates the non-inferiority of therapist-guided iCBT-I, healthcare providers may be more confident recommending this treatment to their patients, contributing to the wider dissemination of CBT-I.

**Trial registration:**

Trial registration number in the German Clinical Trials Register: DRKS00028153 (https://drks.de/search/de/trial/DRKS00028153). Registered on 16th May 2023.

**Supplementary Information:**

The online version contains supplementary material available at 10.1186/s13063-024-08214-6.

## Administrative information

Note: the numbers in curly brackets in this protocol refer to SPIRIT checklist item numbers. The order of the items has been modified to group similar items (see http://www.equator-network.org/reporting-guidelines/spirit-2013-statement-defining-standard-protocol-items-for-clinical-trials/).

**Table Taba:** 

Title {1}	Investigating non-inferiority of internet-delivered versus face-to-face cognitive behavioural therapy for insomnia (CBT-I): a randomised controlled trial (iSleep well)
Trial registration {2a and 2b}.	Trial registration number: DRKS00028153, German Clinical Trials Register. Registered on 16 May 2023.
Protocol version {3}	28 February 2023, version 4.
Funding {4}	Funded by the German Research Foundation (Deutsche Forschungsgemeinschaft; DFG) – Projektnummer: 422022593.

## Introduction

### Background and rationale {6a}

Insomnia disorder is defined as difficulties initiating and/or maintaining sleep and/or early morning awakening accompanied by daytime impairment [1]. To meet diagnostic criteria, the symptoms must occur at least three times per week and persist for a minimum of 3 months [1]. In Europe, approximately 10% of adults meet the criteria for insomnia disorder, with prevalence rates varying between 5.7 and 23.1% across different countries [2]. Insomnia is associated with reduced quality of life [3]. It also increases the risk of cardiovascular diseases [4, 5] and mental disorders, especially depression and anxiety disorders [6–8]. Furthermore, economic costs arise from both absenteeism and reduced productivity while at work (i.e., presenteeism) [9], along with increased healthcare utilisation [10, 11].

Clinical guidelines in Europe and the United States of America (USA) recommend cognitive behavioural therapy for insomnia (CBT-I) as first-line treatment for the disorder [12–15]. This multicomponent treatment consists of psychoeducation, sleep restriction therapy, stimulus control therapy, cognitive therapy, and relaxation techniques [16]. Unfortunately, treatment recommendations do not align with actual clinical practice. In reality, most patients with insomnia are prescribed hypnotic medication or sedating antidepressants [2], even though their long-term use is not recommended for insomnia, given side effects, risk of dependence or addiction, and questionable long-term efficacy [15].

Implementing CBT-I in routine clinical care poses a significant healthcare challenge. Internet-delivered CBT-I (iCBT-I) has the potential to make guideline-recommended therapy more accessible to people suffering from insomnia [17]. Besides improved accessibility, iCBT-I might have further advantages. For example, patients can complete the programme at their own pace, at any time and from anywhere with no travel expenses, and barriers associated with the stigma of mental disorders might be reduced [18, 19]. However, evidence on the non-inferiority of iCBT-I, relative to face-to-face treatment, remains insufficient.

Meta-analyses demonstrate moderate to large effect sizes for face-to-face CBT-I [20] and iCBT-I [21] compared to waitlist and non-active control groups with respect to sleep-related outcomes. Although results from these meta-analyses provide a useful estimate for comparative efficacy, conclusions are limited as the two CBT-I delivery formats were rarely compared directly within the same trial. To date, only limited evidence exists directly comparing face-to-face and internet-delivered CBT-I [22], including just few randomised controlled trials (RCTs) [23–26]. Findings from these studies are inconclusive with respect to the two treatment formats’ relative efficacy.

Two studies have sought to test the non-inferiority of iCBT-I, using either individual or group face-to-face CBT-I as comparison conditions. One of these trials investigated face-to-face group CBT-I by assuming a non-inferiority margin of 4 points on the Insomnia Severity Index (ISI; [27]) and confirmed the non-inferiority of therapist-guided iCBT-I in a sample of 48 patients [23]. However, it could be argued that the non-inferiority margin of 4 points on the ISI is too liberal, as a 4.6-point difference already indicates a clinically meaningful effect [28]. Furthermore, group-delivered therapy is not treatment-as-usual in Germany, as psychotherapy is predominantly provided in an individual treatment format. A stricter non-inferiority margin was applied in the second study by Kallestad et al. [25], using 2 points on the ISI. Here, the non-inferiority of iCBT-I without personal guidance by a therapist was not supported when compared to individual face-to-face CBT-I in a sample of 101 patients. This might be explained by the fully automated digital CBT-I condition, as other research indicates that iCBT-I should be provided with therapists’ support to achieve optimal results [29, 30] and greater acceptance by patients [29].

Two more trials compared the two therapy formats directly, though neither study specified a non-inferiority margin. In a trial by Lancee et al. [24], 30 patients were treated with face-to-face CBT-I by one experienced therapist, while another 30 patients received an iCBT-I programme with support from Masters-level students. On average, the face-to-face treatment led to an additional reduction in insomnia severity by 4.6 points, indicating a clinically meaningful advantage over iCBT-I [28]. In the second study, a trial among active duty military personnel that hypothesised the superiority of face-to-face CBT-I, a greater reduction on the ISI by 3 points was found relative to a newly developed, unguided iCBT-I approach [26]. The difference, however, was non-significant, which might be attributed to only 53% of the planned sample size being recruited, limiting the study’s statistical power.

Overall, evidence on the non-inferiority of iCBT-I is limited to date because sample sizes have been comparatively small (e.g. [23, 24]), and non-inferiority margins have either been not specified (e.g. [24, 26]) or questionably large (e.g. [23]). Moreover, therapists in each treatment arm had different levels of qualification [24], or therapist support was not considered at all [25]. Additionally, previous studies did not demonstrate that treatment content was equivalent [25] in the two treatment formats, and it is unclear whether treatments were conducted in settings representative of treatment in routine clinical care (e.g. [23, 24]). Therefore, consideration must be given to whether usual care is provided through group or individual CBT-I in the respective health systems to ensure the practical applicability of results.

Hence, there is a need for an RCT with rigorous methodology. Besides the limitations of previous clinical trials, numerous patients and practitioners continue to hold the belief that face-to-face treatments yield better outcomes than internet-delivered interventions, and there are concerns about the efficacy of the latter [31]. If a well-executed trial demonstrates the non-inferiority of iCBT-I, relative to face-to-face CBT-I, physicians and healthcare providers might refer their patients for iCBT-I with increased confidence and frequency, which would contribute to wider dissemination of this first-line insomnia treatment.

### Objectives {7}

This trial’s primary objective is to investigate the non-inferiority of therapist-guided iCBT-I versus face-to-face CBT-I using the primary endpoint, the Insomnia Severity Index (ISI; [27]) after treatment completion (10 weeks after randomisation). This will be investigated in an adequately powered sample in routine clinical care, ensuring the same therapeutic content and same therapist qualification level in both interventions. It is hypothesised that therapist-guided iCBT-I is non-inferior to individual face-to-face CBT-I. Secondary objectives of this trial are: (1) to perform a health-economic evaluation of the two interventions and (2) to systematically explore potential benefits and disadvantages associated with iCBT-I.

### Trial design {8}

This study—a randomised controlled non-inferiority trial conducted with two parallel groups (allocation ratio 1:1)—will compare therapist-guided iCBT-I and traditional face-to-face CBT-I.

### Methods: patients, interventions and outcomes

#### Study setting {9}

Patient recruitment started in June 2023 and is taking place in community and academic hospitals and outpatient clinics in Germany specialised in sleep medicine, psychiatry, psychosomatic medicine, or clinical psychology. Ethics approval for the study was obtained from the Ethics Committee of the University of Freiburg Medical Centre. The trial has been registered at the German Clinical Trials Register (DRKS00028153).

#### Eligibility criteria {10}

Inclusion criteria are as follows: (a) age ≥ 18 years; (b) DSM-5 diagnosis of insomnia disorder; (c) access to a computer and the internet; (d) home address not further than a 1-h commute to the nearest study centre; (e) fluent use of German; (f) written informed consent for study participation.

Exclusion criteria are as follows: (a) history of an additional sleep disorder (e.g. moderate or severe sleep apnoea syndrome, restless legs syndrome, narcolepsy); (b) severe or unstable psychiatric disorders (organic, including symptomatic, mental disorders (ICD-10: F00-F09), substance use disorders (ICD-10: F10-F19), schizophrenia, schizotypal and delusional disorders (ICD-10: F20-F29), severe major depressive disorder (ICD-10: F32.2, F32.3, F33.2, F33.3), or other psychiatric disorders clinically assessed as severe) or medical conditions requiring immediate treatment that can impact outcome variables or may be negatively affected by sleep restriction therapy (e.g. epilepsy, bipolar disorder, NREM parasomnia); (c) acute suicidality; (d) pregnancy; (e) ongoing psychotherapy or being on a waiting list for psychotherapeutic treatment; (f) participation in another clinical trial up to 30 days before or during participation in this study.

#### Who will take informed consent? {26a}

During the recruitment period, 16 study centres will recruit participants from patients seeking treatment for insomnia at these centres. Here, potentially eligible patients will receive verbal and written information about the study through a study therapist.

The screening procedure (~ 45 min) includes a face-to-face semi-standardised interview consisting of a detailed sleep history, as well as screening questions regarding psychiatric and medical conditions. In addition, all current sleep and psychopharmacological medications will be recorded. Written informed consent is mandatory for study participation. Consent can be withdrawn at any time without providing a reason.

#### Additional consent provisions for collection and use of patient data and biological specimens {26b}

Patients will be asked to provide their optional additional consent for merging their data with data from a survey with the therapists. In this survey, therapist variables (e.g. experience with iCBT-I, potential benefits and disadvantages of internet-delivered therapy for their therapeutic work) will be collected and examined as potential predictors of treatment effects. This informed consent is entirely voluntary. Patients opting to participate will receive identical treatment as those who choose not to give their consent. Refusal to grant consent will not result in any disadvantages for the patients. No biological specimens will be collected.

### Interventions

#### Explanation for the choice of comparators {6b}

In this non-inferiority trial, the control group will receive the first-line evidence-based treatment for insomnia in Germany, which is face-to-face CBT-I [15]. Therefore, the requirements of the Declaration of Helsinki are fulfilled, which states that “the benefits, risks, burdens, and effectiveness of a new intervention must be tested against those of the best proven intervention” [32].

### Intervention description {11a}

Both therapist-guided iCBT-I and face-to-face CBT-I are based on a published and widely used German-language CBT-I manual [33]. Thus, the two formats are identical in content and encompass the following CBT-I core components: (a) psychoeducation, (b) sleep restriction therapy, (c) stimulus control therapy, (d) cognitive therapy, and (e) relaxation techniques. Both formats consist of six sessions lasting 50 min each. The CBT-I components are delivered in the same order. In both groups, treatment is considered to be in accordance with the protocol if (1) at least 4 of the 6 scheduled sessions took place within the specified 10 weeks after randomisation, (2) no additional psychotherapeutic treatment was sought, and (3) there has been no increase in psychiatric medication. All therapists will be certified psychological or psychiatric psychotherapists for behavioural therapy with expertise in sleep medicine, or psychotherapy trainees supervised by certified psychological or psychiatric psychotherapists for behavioural therapy with expertise in sleep medicine, reflecting the current situation of insomnia treatment in Germany. All therapists will provide both treatments. To facilitate a standardised procedure and the equivalence of content, treatment manuals for both CBT-I conditions will be used by therapists, comprising templates and boilerplates (therapist-guided iCBT-I) and example formulations for psychoeducational information plus exercise sheets (face-to-face CBT-I). Table 1 summarises the content of the six sessions, which will be the same for both treatment conditions.

**Table 1 Tab1:** Session content of the face-to-face and therapist-guided iCBT-I

Session	Main objectives	Content / exercises
1. My good start	• Receiving an overview of the therapy (face-to-face or internet-delivered); defining therapy goals; learning about sleep and insomnia	• Psychoeducation on sleep & insomnia • Defining **p**recipitating, **p**redisposing, and **p**erpetuating factors (3-P model) • Learning sleep hygiene rules • Becoming familiar with the sleep diary (app) • Implementing small and larger relaxation activities in everyday life
2. Renewing the sleep–wake rhythm	• Being introduced to the behavioural components of CBT-I	• Reviewing the relaxation and sleep hygiene activities • Understanding sleep restriction and stimulus control and how to combine them • Determining the bedtime window • Learning tips and tricks for implementing sleep restriction and stimulus control
3. Strengthening the sleep schedule	• Dealing with adverse effects and challenges of sleep restriction and stimulus control; maintaining motivation	• Reviewing implementation of sleep restriction and stimulus control • Adjusting the bedtime window • Dealing with adverse effects and handling challenges • Motivating to keep going • Introducing the first relaxation technique: Progressive Muscle Relaxation (PMR)
4. Dealing with worries and ruminations	• Learning how to deal with sleep-disturbing thoughts and ruminations	• Reviewing implementation of sleep restriction and stimulus control & adjusting the bedtime window • Identifying and challenging dysfunctional beliefs about sleep • Introducing two cognitive techniques: worry chair; thought diary • Introducing a second relaxation technique: body scan
5. Letting go of worries and ruminations	• Trying out a metacognitive technique and another relaxation technique	• Reviewing implementation of sleep restriction and stimulus control & adjusting the bedtime window • Reviewing cognitive techniques’ implementation • Introducing a third cognitive technique: allowing thoughts to come and go (imagination technique) • Introducing a third relaxation technique: mental image of calmness
6. Empowered into the future	• Consolidating and looking back at what has been learned; making a plan for the future	• Reviewing implementation of sleep restriction and stimulus control & adjusting the bedtime window • Reviewing experiences and changes over the past weeks • Relapse prevention: making a plan regarding which methods will be pursued further • Answering open questions

The therapist-guided iCBT-I will be delivered via an access-controlled online platform [34] designed as an interactive website that includes video clips, written information, graphical illustrations, written and audio exercises, examples of other (fictional) patients, and an app-based sleep diary. It is a revised version of an intervention initially developed for workers suffering from insomnia, which we adapted to the routine care setting. The original intervention has been positively evaluated in three randomised controlled trials [35–37]. Therapists have access to their patients’ data and provide written feedback after each completed session (e.g. validating exercises patients completed within the sessions, motivating patients to implement exercises, like sleep restriction therapy, in their daily lives and/or providing additional information). Therapists are advised to provide feedback within two working days and to spend no more than 60 min for writing their feedback for one session.

In the face-to-face CBT-I condition, therapists and patients together work out the CBT-I components. For example, therapists provide information (e.g. psychoeducation about sleep and insomnia) and introduce exercises (e.g. sleep restriction therapy) that patients will be asked to implement in their daily lives. Psychoeducational elements, therapy exercises, and media (e.g. audio relaxation exercises) are the same as those used with the iCBT-I. Patients receive a paper and pencil sleep diary, which is commonly used in routine care CBT-I.

### Criteria for discontinuing or modifying allocated interventions {11b}

One or more of the following circumstances may lead to discontinuation of intervention participation for an individual patient: (a) withdrawal of the patient’s consent, (b) loss of contact with the patient, (c) death of the patient, or (d) other unforeseeable circumstances that would endanger the patient’s health if they continued to participate in the intervention.

### Strategies to improve adherence to interventions {11c}

Adherence—encompassing each patient’s implementation of CBT-I elements and general session attendance—will be documented by therapists in both intervention arms. In cases of non-attendance at a session, therapists will either send written reminders (iCBT-I), call patients by telephone, or send an email (face-to-face CBT-I).

### Relevant concomitant care permitted or prohibited during the trial {11d}

Patients will be asked not to begin any further psychotherapy or new psychiatric/sleep medication, and not increase their psychiatric/sleep medication during study participation. If patients begin another psychotherapy or begin/increase psychiatric/sleep medication during study participation, they may continue with the intervention they were allocated to, but will not be included in the per-protocol analysis (see section “Statistical methods for primary and secondary outcomes {20a}”).

### Provisions for post-trial care {30}

As CBT-I is usually highly effective, no special services are planned after study participation. Patients are encouraged to contact their study centre in case of adverse events or if post-trial care is needed (e.g. non-remitters, non-responders, dropouts).

### Outcomes {12}

An overview of primary, secondary, economic, and exploratory outcomes is available in Fig. 1.

**Fig. 1 Fig1:**
[figure not shown]
Study schedule of enrolment, interventions, and assessments

#### Primary outcome

The primary study outcome will be insomnia severity at post-intervention, assessed using the Insomnia Severity Index (ISI; [27]), a questionnaire that is commonly used in insomnia research [20, 29, 38] and clinical care [15]. Insomnia severity will be assessed at all measurement points (baseline, post-intervention 10 weeks after randomisation, and follow-up 6 months after randomisation). The ISI questionnaire consists of seven items, each answered on a 5-point Likert scale with response options ranging from 0 to 4 and a total score ranging from 0 to 28. In several studies, the ISI has demonstrated good internal consistency with *α* ranging from 0.70 to 0.90 [27, 28, 39]. For all measurement points, total scores will be calculated.

#### Secondary outcomes

Secondary outcomes will be assessed at all measurement points (baseline, post-intervention 10 weeks after randomisation, and follow-up 6 months after randomisation).

Fatigue severity will be measured using the Fatigue Severity Scale (FSS; [40]), comprised of nine items, each rated on a 7-point Likert scale ranging from 1 to 7. The total score ranges from 9 to 63. Internal consistency is good, with *α* = 0.88 [40].

Depression-related symptom severity will be measured using the 9-item version of the Patient Health Questionnaire (PHQ-9; [41]), with response options ranging from 0 to 3, a total score from 0 to 27, and a good *α* of 0.89.

Health-related quality of life will be assessed using the Assessment of Quality of Life (AQoL-6D; [42]), a questionnaire comprised of 20 items that measure six domains (independent living, pain, senses, mental health, coping, relationships). A total score can be calculated across all domains, ranging from 20 to 99. The domains’ reliability ranges from *α* = 0.50 (senses) to *α* = 0.86 (independent living; [42]). Patients’ health (range 0 to 100) will be measured using the slider bar item of the European Quality of Life 5 Dimensions 5 Level questionnaire (EQ-5D-5L [43]).

Daylight exposure will be assessed with a self-developed 5-item questionnaire adapted from the item on daylight exposure of the Munich Chronotype Questionnaire [44]. These five items assess how much time patients have been spending in daylight, on average, at five different time periods during the day (in the early morning (before 8.00 a.m.), later morning (8.00–11.59 a.m.), noon (12.00 p.m. to 2.59 p.m.), afternoon (3.00 p.m. to 5.59 p.m.), evening (6.00 p.m. and after)) over the past 7 days. Total time spent in daylight will also be calculated (see Appendix 1 for further details).

Patients’ physical activity level (i.e., time spent in vigorous- and moderate-intensity activity, walking, and sedentary activity) will be measured using the International Physical Activity Questionnaire – Short Form (IPAQ-SF; [45]). The IPAQ-SF is comprised of seven items that ask individuals to indicate both the number of days and average time over the past week that they have spent at each activity level. A total physical activity level will be estimated by weighting the reported minutes per week within each activity category by a metabolic equivalent (MET) energy expenditure estimate assigned to each activity category (e.g. cycling at vigorous intensity = 8, walking at moderate intensity = 3.3, sitting = 1; see [45]). The weighted MET-minutes per week will be calculated as duration × frequency per week × MET intensity. Test–retest reliability has been found to be very good, with Spearman’s *ρ* = 0.80 [45].

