## Statistical methods

### Statistical methods for primary and secondary outcomes {20a}

#### Efficacy

The primary efficacy analysis will be performed in the per-protocol set, excluding patients with major protocol violations since it is generally recognised that “in an equivalence or non-inferiority trial, use of the full analysis set is generally not conservative” (European Medicines Agency—CPMP/ICH/363/96, Sect. 5.2.3, p. 26). For sensitivity analysis, the same analysis will be performed according to the intention-to-treat principle, based on the full analysis set, including all randomised patients with their original treatment allocation. The effects of internet-delivered and face-to-face CBT-I—with respect to the primary endpoint ISI at post-intervention—will be tested within a linear mixed model for repeated measures with corresponding two-sided 95% confidence intervals (CIs). The model will include treatment and study centre as independent variables. In cases involving low recruitment rates at specific centres, additional sensitivity analyses will be performed. The one-sided test of non-inferiority (internet-delivered versus face-to-face CBT-I) at a significance level of 2.5% will be based on the two-sided 95% CI from the mixed model for repeated measures. The null hypothesis will be rejected if the lower limit of the CI for the difference lies entirely above -1.5 points.

If non-inferiority is concluded, a test for superiority of therapist-guided iCBT-I versus face-to-face CBT-I will be conducted. For this, the primary analysis will be repeated in the full analysis set. If the resulting two-sided 95% CI lies entirely below zero, superiority of therapist-guided iCBT-I versus face-to-face CBT-I will be concluded. As this is a closed test procedure, it will not be necessary to adjust the significance level *α* (see “Points to consider on switching between superiority and non-inferiority” EMA—CPMP/EWP/482/99). Analysis in the mixed model for repeated measures will permit valid inferences under the “missing at random” assumption, which seems justified since we expect that most of the missing data will be absent for reasons probably unrelated to the missing outcomes. Secondary endpoints will be analysed in a fashion similar to the primary outcome, using regression models, as appropriate, for the respective type of data. Treatment effects will be calculated using two-sided 95% CI.

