## Trial status

Patient recruitment started in June 2023. The current protocol is version 4 of 28–2-2023. Presently (26 February 2024), we have enrolled 106 patients. Patient recruitment is estimated to be completed by roughly December 2024.

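### The daylight-exposure outcome is bounded by day length, but the model terms named carry nothing for date; a day-length covariate would gain precision at almost no cost

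*Protocol article*

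**What the plan says.** Under Secondary outcomes, the article describes a self-developed questionnaire on daylight: "These five items assess how much time patients have been spending in daylight, on average, at five different time periods during the day". The windows are fixed by the clock. The first covers the time before 8 a.m., three cover the day, and the last is given as "evening (6.00 p.m. and after)) over the past 7 days". A sum is also formed: "Total time spent in daylight will also be calculated". Like the other secondary outcomes, this one is collected at baseline, 10 weeks and 6 months after randomisation.

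Under Efficacy, the sentence on the primary ISI model reads: "The model will include treatment and study centre as independent variables". For the rest: "Secondary endpoints will be analysed in a fashion similar to the primary outcome", by regression models chosen as suits the type of data. The article mentions season, calendar date and day length nowhere.

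Under Trial status: "Patient recruitment started in June 2023", with completion expected around December 2024. Under Sequence generation, allocation is 1:1 in blocks of varying size within each centre.

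**The concern.** How long a patient can spend in daylight depends on the date as well as on behaviour. A patient randomised in mid-June answers the baseline questionnaire near the longest day and the month-6 questionnaire near the shortest; for mid-December the order is reversed. Recruitment over about 19 months puts every season into every visit.

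A model with only treatment and centre leaves this seasonal spread in the residual. The price is a wider confidence interval for the between-arm difference in daylight exposure. A second, softer risk concerns reporting: a table of raw means by visit would invite readers to take a change that follows the calendar for a change in behaviour.

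**Working it through.** **Figures in the plan.** The article gives no standard deviation, effect size or power for daylight exposure, so there is nothing to reproduce for this outcome. The sample size rests on the ISI alone. Its 191 per arm reproduces (noncentral t power 0.9013 at 191 and 0.8999 at 190, for margin 1.5, SD 4.5, one-sided 2.5%) and plays no part below.

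**Inputs.** From the article: the clock windows, the visit times, the recruitment period, centres throughout Germany, and 382 patients analysed. Assumed: sites between 48 and 53.5°N and between 7.8 and 13.4°E; sunrise to sunset counted as daylight; legal clock time.

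**Step 1, available daylight.** With latitude φ and solar declination δ, cos H = (sin(−0.833°) − sin φ sin δ) / (cos φ cos δ), and day length = 2H/15 hours.
- At 51°N in June (δ = 23.44°): cos H = (−0.0145 − 0.3091)/0.5774 = −0.561, H = 124.1°, day length 16.5 h.
- At 51°N in December (δ = −23.44°): cos H = (−0.0145 + 0.3091)/0.5774 = 0.510, H = 59.3°, day length 7.9 h.

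Cutting each day at the window limits gives, across the assumed sites, no sun after 6 p.m. on 116 to 140 days a year and none before 8 a.m. on 50 to 78 days.

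**Step 2, movement between visits (51°N).**

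| Randomised | Baseline | Week 10 | Month 6 |
|---|---|---|---|
| mid-June | 16.5 h | 14.1 h | 8.0 h |
| mid-September | 12.8 h | 8.6 h | 11.8 h |
| mid-December | 8.0 h | 10.4 h | 16.5 h |

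Over mid-month enrolment dates, one patient's ceiling moves by −4.4 to +4.5 h at week 10 and by −8.5 to +8.5 h at month 6. Averaged over even recruitment from June 2023 to December 2024, the means are 12.3, 11.5 and 12.2 h, so most of this cancels.

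**Step 3, loss of precision at week 10.** Over that recruitment period the SD of available daylight at week 10 is 2.81 h. Suppose a patient uses a fraction k of it, with residual SD s. Then R² = (2.81k)² / [(2.81k)² + s²], and adjustment narrows the interval by 1 − √(1 − R²). Both k and s are assumptions.

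| k | s (h) | R² | Interval narrower by |
|---|---|---|---|
| 0.1 | 2.0 | 1.9% | 1% |
| 0.1 | 1.5 | 3.4% | 2% |
| 0.1 | 1.0 | 7.3% | 4% |
| 0.2 | 2.0 | 7.3% | 4% |
| 0.2 | 1.5 | 12.3% | 6% |
| 0.2 | 1.0 | 24.0% | 13% |
| 0.3 | 2.0 | 15.1% | 8% |
| 0.3 | 1.5 | 24.0% | 13% |
| 0.3 | 1.0 | 41.5% | 24% |

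Example: k = 0.2, s = 1.5 gives 0.562² / (0.562² + 2.25) = 0.316/2.566 = 0.123, and 1 − √0.877 = 0.064. At R² = 10% the loss is equivalent to 0.10 × 382 ≈ 38 patients.

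**Step 4, bias and coverage.** In 2,000 simulated trials of 382 patients with balanced concurrent allocation, no treatment effect, k = 0.3 and s = 1.5, the mean unadjusted difference was −0.005 h and the 95% interval covered in 95.2%. The SD of the estimate fell from 0.176 to 0.152 h with day length in the model, a reduction of 1 − 0.152/0.176 = 14%, in line with the table.

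**The case against.** The strongest reply is that nothing planned is wrong. The two named terms belong to the ISI model. Secondary models need only be similar and suited to the data, so a date term is not excluded, and the covariates of one secondary outcome are ordinary content for an analysis plan that is not shown. The planned inference is the contrast between arms, which concurrent blocked allocation keeps unbiased with valid coverage. All of this stands. It makes the point advice rather than an error, but it does not remove the gain in precision over the model as described.

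Stronger readings are tempting and should be resisted:
- A reader might infer that season biases the treatment comparison. Step 4 and the allocation scheme say otherwise.
- A reader might infer that the trial will take within-arm change as a treatment effect. The article plans no such analysis.
- A reader might expect a rise in mean daylight at month 6. That appears only if recruitment is cut at the article's status date of 26 February 2024, when 106 of 422 patients were enrolled. Over the planned period there is no rise (12.3 h at baseline against 12.2 h).
- A reader might suppose that both outer windows are dark all winter. The early-morning window lacks sun for only about 7 to 11 weeks, and never if civil twilight counts as daylight, which the article's text does not define.
- A reader might suppose that month 6 always brings a very different day length. Near an equinox the shift is small, about 1 h for enrolment in mid-September.

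**Conclusion.** The point holds as a low-severity improvement to one secondary outcome. Time in daylight is bounded by a quantity that roughly doubles between December and June, and the terms named for the model leave it out. The between-arm estimate stays valid but is less precise than it could be. Adjustment would narrow its interval at week 10 by about 1 to 13% for most of the assumed inputs, and by about 24% in the most extreme combination tried. The size cannot be fixed from the documents: it rests on assumed latitudes, an assumed fraction of daylight used and an assumed residual spread. No stated figure in the article changes.

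**What to change.** In the analysis plan, add to the daylight-exposure model the day length at each questionnaire's completion date as a time-varying covariate; annual sine and cosine terms of that date would serve as well. For the early-morning and evening items, use the daylight available within that window instead of the whole day. State that unadjusted within-arm change in daylight exposure will not be read as a treatment effect.

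The cost is one or two lines of text and one or two model terms. Questionnaires are completed online, so completion dates should be available, although the article does not say so explicitly. No new data collection is needed.
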